### Outcomes

The primary outcomes of the RCT are as follows:

Weight gain at 16 weeks and 6 months after intervention initiationWHZ at 16 weeks and 6 monthsMUAC at 16 weeks and 6 monthsAnthropometric measurements collected by trained study staff using standardized procedures and calibrated equipment: weight measured using digital weighing scales; height/length using stadiometers or infantometers, as appropriate; and MUAC using standardized MUAC tapes

The secondary outcomes include the following:

Time to nutritional recoveryNutritional status at follow-up, categorized as cured (WHZ>−2 SD), nonresponder (WHZ<−2 SD), or lost to follow-upTransfer to inpatient careClinical signs of infection and morbidity episodes, including fever, diarrhea, and respiratory symptomsRecurrent infections during follow-upHemoglobin levelsAdverse events related to antibiotic therapyMortality

Clinical outcomes and morbidity episodes will be assessed during scheduled follow-up visits through caregiver interviews and clinical examination by trained study personnel. Hemoglobin levels will be estimated using standard laboratory methods. Information related to inpatient referrals, adverse events, and mortality will be documented using study follow-up records.

The exploratory outcomes include the following:

Proportion of children with clinical infections based on clinical evaluation resultsProportion of children with subclinical infections assessed using hs-CRP, procalcitonin levels, blood culture, and urine cultureGrowth in stool culturePatterns of antimicrobial sensitivity and resistance among children with uncomplicated SAMHealth-seeking behavior, antibiotic usage patterns, and care preferences among caregivers of children with uncomplicated SAMChallenges and facilitators in the management of uncomplicated SAM, as perceived by health care providers

Blood, urine, and stool samples will be collected and processed using standard microbiological and laboratory procedures to assess infection status and AMR patterns. Qualitative data will be collected through FGDs and IDIs using semistructured interview guides.

### Covariates and Other Assessments

The following covariates will be assessed:

Day care absenteeismParental absenteeismMental health status of parentsSocioeconomic statusDomestic violenceFood consumption patternsHousehold food insecurity

Information about day care absenteeism will be obtained from Integrated Child Development Services records. Socioeconomic status will be assessed using the BG Prasad socioeconomic scale. Dietary intake will be assessed using a 24-hour dietary recall method. Household food insecurity will be assessed using the Household Food Insecurity Access Scale and categorized into food-secure, mildly food-insecure, moderately food-insecure, and severely food-insecure households. Questions adapted from the NFHS-5 women’s questionnaire will be used to assess domestic violence.

### Data Entry and Analysis

#### Phase 1

Data will be entered into the Epicollect5 mobile app and analyzed in Stata version 18.0 software. Continuous variables (age, weight, height, WBC count, ESR, hs-CRP, procalcitonin, and colony-forming units) will be expressed as mean (SD) or median (IQR) based on data distribution. Categorical variables (clinical infection, subclinical infection, and AMR) will be expressed as percentages. The association between independent factors (sociodemographic, health, and nutritional factors) and of clinical/subclinical infection and AMR outcomes will be analyzed using chi-square tests, *t* tests, or Mann-Whitney *U* tests. Multivariate analysis using log-binomial regression will be performed to adjust for confounders. *P*<.05 will be considered statistically significant.

#### Phase 2

English transcripts will be prepared within 24 hours of conducting an IDI/FGD. Qualitative data will be analyzed in Atlas Ti software. First, complete transcripts will be read by the investigators to ensure immersion, initial codes will be generated inductively using inductive coding in Atlas.ti software, and the codes will be iteratively refined through discussions and organized into subcategories (subthemes) and higher-order categories (themes) in line with reflexive thematic analysis principles [42]. An audit trail (coding decisions, evolving codebooks, and notes from analytical discussions) will be maintained throughout the process to support confirmability and dependability. We will also perform data triangulation of qualitative and quantitative data to increase the credibility of the information collected about knowledge, barriers, and facilitators related to antibiotic usage among children with uncomplicated SAM by adopting convergent parallel mixed methods design.

#### Phase 3

Data analysis will be performed in Stata version 18.0 software using intention-to-treat analysis at the end of the study. Per protocol analysis will also be performed as a secondary analysis at the end of the study. Interim analysis will be part of the quality parameter (at the end of the first year). The WHZ and MUAC will be expressed as mean (SD) or median (IQR) with 95% CIs based on data normality. The presence of bilateral pitting edema will be expressed as proportions with 95% CIs. Independent variables (child’s age in months and mother’s age) will be expressed as mean (SD) or median (IQR) with 95% CIs based on data normality. Factors such as education status, type of delivery, and birth complications will be expressed as proportions with 95% CIs. Outcomes such as episodes of acute illness, day care absenteeism, parenteral absenteeism, number of hospital visits, and food consumption will be expressed as mean (SD) or median (IQR) with 95% CIs based on data normality. Outcomes such as the presence of sepsis and mortality status will be expressed as proportions with 95% CIs. The chi-square test will be performed to analyze the association between outcomes and categorical independent variables. An unpaired *t* test (or Mann-Whitney *U* test) will be performed to assess the association between outcomes and continuous independent variables. Poisson regression analysis (bivariate and multivariate) will be conducted to explore the association between dependent and independent factors. Adjusted risk ratios with 95% CIs will be reported for factors included in the multivariate Poisson regression model.

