### Sample Size

#### Phase 1

Bhutta et al [8] reported that the rates of clinical infections among children with complicated SAM vary from 15% to 68%. Considering 50% prevalence of lower respiratory tract infection among children with uncomplicated SAM, 95% CIs, 10% relative precision, 1.5% design effect, 10% nonresponse rate, and 5% type I error, we will require 606 participants aged 6-59 months with uncomplicated SAM.

#### Phase 2

A purposive sampling strategy will be followed to select participants. Primary caregivers of children with uncomplicated SAM will be identified based on their volunteerism and participation. Yadadri Bhuvanagiri District comprises four project areas (Bhongiri, Aler, Mothkur, and Ramanapeta), each consisting of multiple sectors and each sector covering 25 *Anganwadi*s [38]. FGDs are planned at the project level to ensure adequate representation across geographic areas and variations in the distribution of children with uncomplicated SAM. Initially, two FGDs are planned per project area; however, considering the larger geographic coverage and higher caseload in two project areas, an additional FGDs will be conducted in each of these areas based on data flow. In total, 10-12 FGDs will be conducted to capture diversity in experiences and practices across the district. Each FGD will include 8-10 participants.

As the aim is also to explore barriers and facilitators related to the management of children with uncomplicated SAM, IDIs are planned to include service providers across different levels of the health system. This approach reflects the continuum of care, as a child with uncomplicated SAM encounters multiple providers at different points within the health system. Therefore, two IDIs will be conducted in each health care worker group: Accredited Social Health Activist (ASHA), *Anganwadi* teacher (center), ANM (subcenter), MO (PHC), and pediatrician (district hospital and tertiary care center).

The data saturation principle will guide the final number of FGDs and IDIs to be conducted. Saturation will be considered achieved when no new themes, patterns, or insights emerge from successive FGDs or IDIs and when there is redundancy in the information obtained. Data collection and analysis will be undertaken simultaneously to monitor saturation, and additional FGDs or IDIs will be conducted, if required.

#### Phase 3

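### Phase 1 is sized with a design effect, but neither its sampling nor its named analysis contains a cluster unit or variance adjustment to match

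*Protocol article*

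**What the plan says.** **Sample Size, Phase 1.** The calculation starts from "Considering 50% prevalence of lower respiratory tract infection among children with uncomplicated SAM, 95% CIs" and adds "10% relative precision, 1.5% design effect, 10% nonresponse rate". It concludes that "we will require 606 participants aged 6-59 months with uncomplicated SAM". No cluster unit, intracluster correlation (ICC) or reason for the design effect is given.

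**Inclusion and Exclusion Criteria and Study Procedure, Phase 1.** Children are listed from the state tracking system, and every eligible child is to be approached and visited at home. No stage that samples villages, sectors or Anganwadis is described.

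**Data Entry and Analysis, Phase 1.** Infection and AMR are summarised as percentages. For associations, "clinical/subclinical infection and AMR outcomes will be analyzed using chi-square tests", with t or Mann-Whitney tests as alternatives. Then: "Multivariate analysis using log-binomial regression will be performed to adjust for confounders". The significance threshold is 0.05. Confounding is the only stated reason for the regression, and clustering is not mentioned.

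**Study Objectives.** The prevalence of infection, the AMR patterns and their associations with child and household factors form one of the primary objectives.

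**The concern.** A design effect above 1 means that the variance of the prevalence estimate is expected to exceed that from the same number of independent children. Here it raises the requirement before nonresponse by half. The named tests and the log-binomial model, in their usual form, take their reference distributions from independent children. If the planning assumption is true, they understate uncertainty and can reject because of clustering alone. If it is not, the sample was inflated without a stated reason.

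At stake are the precision reported for infection and AMR prevalence, and the error rate for factors that neighbouring children share. The target of 5 percentage points (10% of 50%) was set with the design effect included. An unadjusted interval would therefore claim more precision than the sponsor's own calculation allows.

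**Working it through.** **1. The plan's own figure.** Inputs from Sample Size, Phase 1: p = 0.50, d = 0.10 × 0.50 = 0.05, z = 1.96.

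- n0 = z²p(1−p)/d² = 3.8415 × 0.25/0.0025 = 384.1
- Design effect read as 1.5: 384.1 × 1.5 = 576.2
- With the stated 10% nonresponse: 576.2/0.90 = 640, or 576.2 × 1.10 = 634
- With 5% instead: 576.2/0.95 = 606.5, or 576.2 × 1.05 = 605
- Design effect read literally as 1.5% (1.015), with 10% nonresponse: 433 or 429

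So 606 does not follow from the stated nonresponse rate (a separate matter), but a factor of 1.5 is the only reading that comes near it.

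**2. Half-width at n = 606, p = 0.50.**

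- Unadjusted: 1.96 × √(0.25/606) = 4.0 points
- With design effect 1.5: 4.0 × √1.5 = 4.0 × 1.22 = 4.9 points
- The adjusted interval is 22% wider than the unadjusted one; equivalently, the unadjusted one is 1 − 1/1.22 = 18% too narrow.

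**3. Coverage and rejection by true design effect D.** Coverage of an unadjusted 95% interval = 2Φ(1.96/√D) − 1. Rejection of a true null, for a factor constant within clusters of equal size, = 1 − coverage.

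| D | Coverage | Rejection |
|---|---|---|
| 1.05 | 94.4% | 5.6% |
| 1.10 | 93.8% | 6.2% |
| 1.25 | 92.0% | 8.0% |
| 1.50 | 89.05% | 10.95% |
| 2.00 | 83.4% | 16.6% |

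**4. Factors that are only partly shared.** Beta-binomial simulation with p = 0.50, D fixed at 1.5, and 60 clusters of 10 or 24 clusters of 25 (assumed sizes), 8,000 runs per setting. Rejection of a true null by the ICC of the factor itself:

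- factor ICC 1 (constant within cluster): 11.3% and 11.2%
- factor ICC 0.3: 6.9% and 6.9%
- factor ICC 0.1: 5.7% and 5.6%
- factor ICC 0 (purely individual): 5.2% and 5.1%

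Coverage of the unadjusted prevalence interval was 88.0% to 88.8%. Agreement between the two cluster sizes is no evidence of robustness, because the outcome ICC was set to 0.5/(m − 1) to hold D at 1.5.

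**5. How plausible is 1.5?** D = 1 + (m − 1) × ICC, with m children per cluster. The ICC of 0.05 below is an assumption.

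- Village: about 300 villages (Study Area), so m = 606/300 = 2.02. D = 1.5 needs ICC = 0.5/1.02 = 0.49; an ICC of 0.05 gives D = 1.05.
- Anganwadi: four project areas, each with multiple sectors of 25 Anganwadis (Sample Size, Phase 2), so at least 4 × 2 × 25 = 200 and m is at most 606/200 = 3.03. D = 1.5 then needs ICC = 0.5/2.03 = 0.25 or more; an ICC of 0.05 gives D of at most 1.10.
- Larger units: m = 10 needs ICC 0.056, and m = 25 needs 0.021. The number of sectors is not given, so m per sector is unknown.

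**The case against.** The strongest reply is that the design effect may be no more than a planning margin. Every eligible child is to be contacted, so the usual source of a design effect, sampling of clusters, is absent. On the document's own counts there are about two children per village and three or fewer per Anganwadi, so the real effect could be slight. A condensed article may also leave the variance estimator to a fuller plan.

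Much of this stands, and it rules out several stronger readings that a reader might infer:

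- *That the plan itself says its data are clustered.* It gives a number, without unit, ICC or rationale.
- *That the prevalence intervals will cover 89%.* The Phase 1 analysis promises only percentages. Confidence intervals for Phase 1 appear only in the sizing sentence, so no unadjusted interval has been specified.
- *That the tests have an 11% error rate.* That figure needs a true design effect of 1.5 and a factor constant within cluster. No area-level factor is named, and the items under Covariates and Other Assessments are child, parent or household measures.
- *That the log-binomial model is fixed with independence-based standard errors.* The text is silent on this.
- *That the two sections cannot both stand.* A cautious inflation of the sample does not strictly contradict a simpler analysis.

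The mismatch itself remains. The article does not leave the methods open: it names the tests and the threshold, and these have no counterpart to an assumption that added half to the requirement. Contacting every eligible child does not make neighbours' outcomes independent.

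**Conclusion.** The point holds as a mismatch between planning and analysis in a primary objective, with a conditional effect. At the sponsor's own planning value of 1.5, unadjusted inference would give about 89% coverage for prevalence, with a half-width of 4.0 instead of 4.9 points. Rejection of a true null would be up to about 11% for factors constant within a cluster, about 5-7% for child or household factors that are weakly to moderately shared, and about 5% for purely individual ones. At a design effect of 1.05, the loss is negligible: 94.4% coverage and at most 5.6% rejection.

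These figures rest on reading 1.5% as 1.5, on equal cluster sizes, and on a two-sided 5% level. The documents do not show which design effect will apply. The gap is worth closing because the remedy is cheap and the cluster unit is best recorded while Phase 1 data are being collected.

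**What to change.** Amend the Phase 1 part of Data Entry and Analysis to:

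- name a cluster unit (for example Anganwadi, village or sector) and record it for each child; the four project areas are too few to serve as clusters for robust standard errors;
- report prevalence and AMR proportions with survey or cluster-robust 95% intervals;
- use design-based tests (Rao-Scott chi-square, or cluster-adjusted regression in place of t and Mann-Whitney tests);
- fit the log-binomial model with cluster-robust standard errors.

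In Sample Size, Phase 1, print the design effect as 1.5 and state the unit and ICC behind it. If the sponsor instead holds that contacting every eligible child leaves no meaningful clustering, that section should justify the design effect on other grounds or drop it.

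The cost is a few sentences, one recorded field and standard options in Stata, the software already named. The Anganwadi is probably recoverable, since Anganwadi teachers identify the children, although the article does not say that the tracking list carries it. Intervals become up to about 22% wider if clustering is as large as planned, and change little if it is negligible.

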## Introduction

### Background

Acute malnutrition is defined as a condition characterized by a severe nutrient deficit due to inadequate intake of food or the inability of the body to properly absorb essential nutrients [1]. Worldwide, 45.4 million children aged <5 years have wasting [2]. In India, the National Family Health Survey (NFHS)-5 reported a 19.3% burden of wasting and a 7.7% burden of severe wasting [3]. Although the burden of wasting remains almost constant, there is an increase in severe wasting compared to NFHS-4 and NFHS-3 [3-5]. Severe wasting indicates severe acute malnutrition (SAM) and is defined as a weight-for-height z-score (WHZ) of <−3 SD, a mid-upper arm circumference (MUAC) of <115 mm, or bilateral pitting pedal edema [6].

From the management perspective, SAM is further classified into complicated and uncomplicated SAM. Children with complicated SAM exhibit no appetite or have medical complications, while those with uncomplicated SAM have a successful standard appetite test and no fever, clinical infections, or complications [7]. Children with both complicated and uncomplicated SAM have a higher risk for acute infections, such as pneumonia, diarrhea, and sepsis, which triples the mortality risk: a few reported reasons are a weakened immune system, altered gut microbiota, poverty, food insecurity, and inadequate access to health care [8,9]. The fatality rate among children with SAM receiving inpatient care ranges from 3.4% to 35%. These data show that 3.5 million deaths are estimated among children in India aged <5 years [10].

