Rao et al [34] reported the WHZ mean (SD) as –1.29 (0.84) in the amoxicillin group and –1.45 (0.93) in the control group at the end of 2 weeks of intervention. Considering these values, with 95% CI and 80% power, we will require 480 participants in each group. Considering logistic issues, feasibility, and long follow-up, we will recruit 250 children aged 6-59 months with uncomplicated SAM per group.

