**Figure 1 figure1:**
[figure not shown]
RCT CONSORT flow diagram for recruitment, follow-up, and endline assessment of participants in the study. CBC: complete blood count; CONSORT: Consolidated Standards of Reporting Trials; DST: drug susceptibility testing; ESR: erythrocyte sedimentation rate; FGD: focus group discussion; hs-CRP: high-sensitivity C-reactive protein; IDI: in-depth interview; RCT: randomized controlled trial; SAM: severe acute malnutrition.

**Table 1 table1:** Timepoints and activities to be carried out during the study.

Activity	Baseline	Enrollment to RCT^a^ (within 7 days of collecting baseline data)	Telephonic follow-up at 15, 45, 75, and 105 days (plus 5 days allowed at each timepoint)	Physical follow-up at 30, 60, 90, 120, and 180 days (plus 5 days allowed at each timepoint)
Consent; appetite test; sociodemographic, nutritional, and health-related information obtained through questionnaires during face-to-face interviews + 4 mL^b^ of blood sample, urine sample, and stool sample for CBC^c^, ESR^d^, culture, DST^e^, hs-CRP^f^, procalcitonin, and anthropometry (height, weight, MUAC^g^)	✓	—^h^	—	—
RCT eligibility assessment, randomization and antibiotic distribution, and IFA^i^ syrup distribution in the case of anemia	—	✓	—	—
Weight, height, MUAC, symptoms of adverse events, any illness, and treatment details	—	—	—	✓
Symptoms of adverse events, any illness, and treatment details	—	—	✓	✓

^a^RCT: randomized controlled trial.

^b^Biological samples will be collected from 606 study participants.

^c^CBC: complete blood count.

^d^ESR: erythrocyte sedimentation rate.

^e^DST: drug susceptibility testing.

^f^hs-CRP: high-sensitivity C-reactive protein.

^g^MUAC: mid-upper arm circumference.

^h^Not applicable.

^i^IFA: iron folic acid.

#### Phase 1

A list of children with uncomplicated SAM will be obtained from the NHTS website through district stakeholders. The children will be visited at their homes to confirm their diagnosis and malnutrition category and will be enrolled into the study after obtaining informed consent from the caregivers. The children’s sociodemographic, nutritional, and health-related information will be obtained through questionnaires and interviews. Under a sterile environment, 4 mL of blood sample will be taken from each child. Two sterile containers will be given to the children to collect urine and stool samples, and those samples will be collected from the caregivers the following day.

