### Operational Definitions

Children with uncomplicated SAM are clinically well (ie, without signs of infection) and with a retained appetite (passed the appetite test), which is considered indicative of the absence of severe metabolic disturbance. SAM is defined as WHZ<–3 SD of the median WHO child growth standards and/or by the presence of bilateral pitting edema. Nonresponse to treatment is defined as children who do not meet discharge criteria (WHZ>–2 SD) after 4 months.

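### The secondary outcome of cure rests on WHZ alone, so a child with new bilateral edema can have SAM and be cured at the same visit; the promised edema analysis has no clearly listed follow-up data behind it.

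*Protocol article*

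**What the plan says.** All places are in the protocol article.

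- **Operational Definitions.** SAM is WHZ below –3 SD "and/or by the presence of bilateral pitting edema". The Background also lists edema as one of three alternative criteria: "a mid-upper arm circumference (MUAC) of <115 mm, or bilateral pitting pedal edema".
- **Inclusion and Exclusion Criteria, Phase 3.** A child must have no edema to enter the trial. Entry is on WHZ below –3 SD or on a MUAC criterion.
- **Outcomes.** Nutritional status at follow-up, a secondary outcome, counts a child as cured when WHZ is above –2 SD. No other condition is attached. Time to nutritional recovery is also secondary, and its rule is not spelled out.
- **Operational Definitions, nonresponse.** "Nonresponse to treatment is defined as children who do not meet discharge criteria", and the criterion given there is again WHZ above –2 SD, judged after 4 months.
- **Data Entry and Analysis, Phase 3.** "The presence of bilateral pitting edema will be expressed as proportions with 95% CIs".
- **Table 1, physical follow-up.** The listed items are "Weight, height, MUAC, symptoms of adverse events, any illness, and treatment details". Edema is not named.

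**The concern.** Two things do not fit together.

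First, the definition of the disease and the definition of recovery from it disagree. Edema is sufficient for SAM, but its presence does not prevent a child from being scored as cured. Because entry excludes edema, any edema seen in the trial is new and marks deterioration. The outcome rule ignores it.

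Second, the plan commits to analysing edema without saying at which time point, and the follow-up schedule does not name it as a recorded sign. A proportion with a confidence interval needs a yes/no reading for each child at a stated visit.

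At stake is the credibility of the secondary recovery outcome, and of time to recovery if that uses the same rule. Edema fluid also adds weight, so it enters weight gain and WHZ, which are primary outcomes.

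**Working it through.** **1. The definitions side by side**

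Take a trial child at a follow-up visit with bilateral pitting edema and WHZ above –2 SD.

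| Rule | Section | Result |
|---|---|---|
| SAM: WHZ below –3 SD and/or edema | Operational Definitions | has SAM |
| Cured: WHZ above –2 SD | Outcomes | cured |
| Nonresponse: discharge criterion (WHZ above –2 SD) not met after 4 months | Operational Definitions | not a nonresponder |

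Nothing in the article says which result prevails.

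**2. The edema analysis on each reading**

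- Baseline: entry requires no edema, so the proportion is 0 in every arm and the analysis is empty.
- Follow-up: the analysis is informative, but the follow-up row of Table 1 does not name the sign.

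**3. Size of the effect on cure**

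The documents give no incidence, so two inputs are assumptions: e, the proportion who have new edema at the assessment, and s, the share of those whose WHZ is above –2 SD. With the planned 250 per group ("we will recruit 250 children aged 6-59 months with uncomplicated SAM per group"):

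falsely cured children per arm = 250 × e × s; overstatement in points = 100 × e × s.

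| e | s | Children per arm | Points |
|---|---|---|---|
| 0.2% | 1 | 0.5 | 0.2 |
| 1% | 0.5 | 1.25 | 0.5 |
| 3% | 1 | 7.5 | 3 |
| 5% | 1 | 12.5 | 5 |

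Setting s = 1 gives the upper bound.

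**4. Effect on the comparison of cure rates**

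Equal overstatement in all arms creates no false difference. As a worst case, put all of it (d) in one of two arms with equal true cure rates p. The normal approximation to the two-sided 5% test gives

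P(reject) ≈ Φ(z – 1.96) + Φ(–z – 1.96), with z = d / √{[p(1–p) + (p+d)(1–p–d)] / 250}.

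| d | P(reject), p from 40% to 80% |
|---|---|
| 0 | 5% |
| 1 point | 5.6% to 5.9% |
| 2 points | 7.4% to 8.8% |
| 5 points | 20% to 31% |

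Example: p = 0.40 and d = 0.02 give z = 0.02/0.0440 = 0.455 and P = 0.066 + 0.008 = 0.074.

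**5. Effect on mean WHZ**

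The yardstick is the plan's own sample size calculation: –1.29 (0.84) "in the amoxicillin group and –1.45 (0.93) in the control group at the end of 2 weeks of intervention", a difference of 0.16. The common SD is √[(0.84² + 0.93²)/2] = 0.886, and n = 2 × (1.96 + 0.842)² × 0.886² / 0.16² ≈ 482. This reproduces the stated figure to rounding ("with 95% CI and 80% power, we will require 480 participants in each group").

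Assume e of 1% to 3% and fluid worth 0.5 to 1.0 WHZ. One arm's mean then rises by 0.01 × 0.5 = 0.005 to 0.03 × 1.0 = 0.03. That is 3% to 19% of 0.16. With 250 per group the standard error of the difference is √[(0.84² + 0.93²)/250] = 0.079, so the shift is 0.06 to 0.4 standard errors, and only if every case falls in one arm.

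**6. Can fluid alone produce a cure?**

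Not in the typical entrant under these assumptions. Starting below –3 SD, a gain of 0.5 to 1.0 cannot take WHZ above –2 SD. The child must also have made a real gain, or have entered on MUAC with a higher WHZ. So s is likely to be below 1.

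**The case against.** The strongest reply is that this is a wording gap with little numerical weight. No document figure supports any particular incidence or any difference between arms, and edema at entry is excluded. That stands, and it limits the size of the point.

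It can also be said that edema may be recorded anyway. The Outcomes section mentions clinical examination at scheduled visits, Table 1 includes any illness, and operating procedures are not shown. This stands in part. A reader might infer from Table 1 that edema will not be examined at follow-up, but the article does not support that: its table is condensed, and the promised analysis implies some recording. What can be said is that the listed items do not clearly support the analysis. In any case, recording edema would not change the rule for cure, which the article fixes itself.

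Transfer to inpatient care, morbidity and mortality are separate outcomes and may reveal an affected child. They do not override the cured category.

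Two stronger readings are tempting. One is that the primary result is biased toward the arm with more edema. That needs a difference between arms for which the documents give no evidence, and even the extreme case worked above is about 0.4 standard errors in mean WHZ. The other is that a worsening child is scored as recovered through fluid alone. For a child entering below –3 SD this does not follow under the assumed fluid effect.

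Finally, dropping weight or WHZ readings taken with edema from the primary analysis would remove post-randomization data because of a post-randomization event, in tension with the planned intention-to-treat analysis. That objection is right, and the fix respects it.

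**Conclusion.** The point holds as an inconsistency in outcome definition. By the article's own wording a child can have SAM and be cured at one visit, and the edema analysis is either empty at baseline or not clearly supported by the listed follow-up data.

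The effect is probably small and mainly on the secondary recovery outcome. Under assumed incidences of 0.2% to 5%, an arm's cure rate is overstated by at most 0.2 to 5 points, and the upper bound requires every child with edema to have WHZ above –2 SD. The comparison is affected only if edema differs by arm. A false difference of 1 to 2 points leaves the 5% test between about 5.6% and 8.8%; only the extreme of 5 points, all in one arm, would distort it seriously. Bias in the primary weight or WHZ results is possible in principle but is not shown. The change is worth making because the rule as written misclassifies and is cheap to repair.

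**What to change.** 1. Add a yes/no item for bilateral pitting edema to the physical follow-up visits in Table 1, and state in the Phase 3 analysis that the edema proportions refer to those visits.
2. For outcome scoring, count a child as cured only when WHZ is above –2 SD and bilateral edema is absent. Apply the same condition to time to nutritional recovery if it uses the same rule. State in which remaining category a child with WHZ above –2 SD and edema is reported.
3. Keep all weight and WHZ readings in the primary intention-to-treat analysis. Add a sensitivity analysis that leaves out readings taken with edema.
4. Reconcile Operational Definitions, Outcomes, the Phase 3 analysis and Table 1 on how edema bears on recovery. This concerns scoring only; which clinical discharge rule should apply is for the investigators and is not proposed here.

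The cost is one examination item at visits already planned, a few words of definition and one extra analysis. A few children at most would move out of the cured category. The article reports that the start of the randomized phase is delayed, so the change can be made before trial data are collected.
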